#### Baseline survey

At baseline, all participants (i.e., all family members nested in the 150 families) will complete a survey to assess lifestyle behaviors, including diet and physical activity, attitudes towards food and perceived disease risk. This survey will be available in either a paper or online format and takes no longer than 45 min to complete. There are two baseline forms of the questionnaire, one for adults and one for children. The adult version is identical across ethnic groups, with the exception of an acculturation questionnaire which appears in the Italian and Vietnamese versions. As part of their baseline survey all index mothers and fathers will be invited to complete a FHH, which involves indicating disease history for heart disease, diabetes, breast and colorectal cancer for the mothers’ and fathers’ first and second degree relatives. Measures included in the parent and child versions of the baseline are described in Table 1.

**Table 1 Tab1:** Summary of measures included and point of data collection

Families, food and eating survey	Baseline	Endpoint	Adult	Child
Section 1: Cultural identity and background (7 items)				
Country of origin and parents’ origin, language spoken at home.	X		X	X
Section 2: Lifestyle (current behavior determined from previous week)^1^ (13 items)				
Smoking status	X	X	X	
Vigorous Physical Activity:				
• Days per week	X	X	X	X
• Hours/Minutes per day	X	X	X	X
Moderate Physical Activity:				
• Days per week	X	X	X	X
• Hours/Minutes per day	X	X	X	X
Sedentary Behavior:				
• Hours/Minutes per day on a weekday	X	X	X	X
• Hours/Minutes per day on the weekend	X	X	X	X
• Sedentary activities (Children only) – hours per day on a weekday	X	X		X
• Sedentary activities (Children only) – hours per day on a weekend	X	X		X
Family physical activity				
• Days per week	X	X	X	X
• Hours/Minutes per day	X	X	X	X
Serves of fruit per day averaged over previous week	X	X	X	X
Serves of vegetables per day averaged over previous week	X	X	X	X
Number of visits to franchised fast food restaurants in the previous week	X	X	X	X
Serves of high fat and/or high sugar “snacks” per day averaged over previous week	X	X	X	X
Alcohol consumption				
• Days on which alcohol consumed in past week	X	X	X	
• Average number of standard drinks on drinking days	X	X	X	
Section 3: Intended Lifestyle Changes (Minimum 1 item, Maximum 6 items)^2^				
Considering Lifestyle change (yes or no)	X	X	X	X
Areas: Fruit and Vegetable consumption; Physical Activity;	X	X	X	X
Additional areas: Fibre consumption; Alcohol consumption; Smoking	X	X	X	
If yes, identified each area of change and confidence in capacity to change (Self efficacy for Behavior Change) on a 7 point rating scale where 1 is Not at all Confident, 4 is Moderately Confident and 7 is Very Confident.	X	X	X	X
Indicate any areas where lifestyle changes have been made in the last 6 months		X	X	X
Section 4: Food Attitudes (21 items)# (some excluded for children; 16 items)				
Food Life Questionnaire Short Form [53] rated on a 7 point rating scale where 1 is Strongly Disagree and 7 is Strongly Agree	X	X	X	X
Section 5: Disease Risk (10 items)				
Likelihood of talking to doctor about chronic diseases risk in the next 6 months	X	X	X	
Likelihood of talking to family about chronic diseases risk in the next 6 months	X	X	X	
Ratings of perceived lifetime risk for colorectal cancer, breast cancer, heart disease and diabetes	X	X	X	
All rated on a 7 point rating scale where 1 is Not at all Likely and 7 is Extremely Likely. (Don’t Know and Not Applicable provided for each specific disease ratings)				
Perceived contribution of lifestyle factors to disease risk (includes eating habits, alcohol consumption, physical inactivity, genetic factors)	X	X	X	
All rated on a 7 point rating scale where 1 is Not at All and 7 is A Great Deal				
Section 6: Cultural Identity (Italian and Vietnamese participants only)				
Stephenson Multigroup Acculturation Scale (32 items) [54]	X		X	
Ratings of extent of agreement with a series of “I” statements				
All rated on a 4 point rating scale where 1 is False and 4 is True. Not Applicable also provided.				
Section 6 (or 7): Questions about your *own* health history (1 item; 4 diseases)				
Categorical response for heart disease, diabetes, colorectal cancer and breast cancer (includes Don’t Know and Age at diagnosis)	X		X	
Section 7 (or 8): Questions about your *family’s* health history (9 items) (used to compile FHHA; adapted from CDC online Family Healthware Tool)				
Categorical response for heart disease, diabetes, colorectal cancer and breast cancer (includes Don’t Know and Age at diagnosis)	X		X	
Section 8 (or 9): Demographics (12 items)				
Age, gender, height, weight, number of people living in the home, number of children (adults) or siblings (children), adults only: marital status, income (Endpoint only), education (Endpoint only), health insurance (categorical)	X	X	X	X
Social and Cultural Capital (6 items/domains)				
Newspaper most often read (categorical)	X		X	
Television station watched most often (categorical)	X		X	X
Shops from which food is purchased and frequency, choice of 4 including “Other”	X		X	
All rated on a 5 point rating scale where 1 is Never and 5 is all the time				
Recreational activities, choice of 6	X		X	
All rated on a 5 point rating scale where 1 is Never and 5 is daily				
Frequency of direct contact with three groups of people; friend, workmates and neighbors	X		X	
All rated on a 6 point rating scale where 1 is Almost every day and 6 is Don’t have any				
Membership in any of 4 different organizations; religious, recreational, cultural or educational, and “other” community-based (categorical)	X		X	
Endpoint – Additional Measures				
Section 4: Beliefs and Attitudes to Life (28 items)				
Multidimensional Health Locus of Control Scale (18 items) [55]		X	X	
Life Orientation Test – Revised (10 items) [56]		X	X	
All rated on a 5 point rating scale where 1 is Strongly Disagree and 5 is Strongly Agree				
Intervention group only – evaluation of the extent to which Families SHARE information was shared amongst family members		X	X	
Section 5: Disease Risk (15 items)				
Conversations about chronic diseases in the past 6 months with doctor, family member, friends, others	X	X	X	
Ratings of perceived lifetime risk for colorectal cancer, breast cancer, heart disease and diabetes *of child*	X	X	X	
Rated on a 7 point rating scale where 1 is Not at all Likely and 7 is Extremely Likely.				
(Don’t Know and Not Applicable provided for each specific disease ratings)				
Participation in screening for each of the 4 chronic diseases		X	X	
Section 6: Your Family				
Box providing scope for enumeration of people who are considered as family members		X	X	X
Section 7: Family Health History Evaluation INTERVENTION GROUP ONLY (3items; all categorical responding)				
Ability to assess disease risk		X	X	
Sharing of FHHA information		X	X	
Was the FHHA updated after receipt?		X	X	

^1^Section 1 in Endpoint Survey

^2^Section 2 in Endpoint Survey

#### Family social network survey

Approximately 2 weeks after return of the final family member’s baseline survey, each family member will be contacted to arrange a phone interview to gather information on their family social network. A personal, or “egocentric”, approach to data collection will be adopted [48], whereby participants are asked to name the people in their family and answer questions about the types of relationships they have with each family member. Participants will first be asked to enumerate a list of individuals they consider to be “family members”, which can include biological kin, non-biological kin, and “social kin”. Then they are asked to consider the previous 3 months and to identify which of these family members they shared the following specific types of relationships with: with whom they talked to about health and family risk of disease; who encouraged them to eat healthily or unhealthily or made eating specific healthy or unhealthy foods difficult; with whom they exercised, who encouraged them to exercise or who made exercising difficult to engage in; and family members with whom they watched television. Adult participants will also be asked to consider the same 3 month period and identify with whom they consumed alcohol, who encouraged or discouraged consumption, and who made it difficult to consume. The adults will be asked the same questions about smoking (see Table 1).

#### Family health history intervention

Three months after an intervention family has provided the last baseline survey they will receive a health education booklet, entitled ‘Families SHARE’. This will contain a visual family pedigree of the previously identified first and second degree relatives of the index parents with disease markers highlighted for heart disease, diabetes, breast and colorectal cancer. The ‘Families SHARE’ booklet contains a clear description of a family pedigree with guidance to help participants interpret their own and other family members’ risk for disease using the pedigree. In addition, the booklet contains information about genetic and environmental risk for disease along with behavioral and screening recommendations.

The control group of families will receive nothing between baseline and follow-up, and will receive their ‘Families SHARE’ booklet containing their family’s health history upon completion of the study.

#### Endpoint survey

All participating families will be re-contacted 6 months following the completion of baseline for follow-up assessment. This endpoint survey is similar in format to baseline. It will assess eating and exercise behaviors, attitudes towards food and perceived disease risk, health locus of control, optimism, as well as assess intentions to increase healthy behaviors in the future and tap any purposeful changes made or screening activities undertaken in the past 6 months. In addition, adults in the intervention group will be asked questions designed to evaluate the extent to which information from the Families SHARE workbook was shared amongst family members. All children in the trial will complete the same children’s version of the questionnaire (see Table 1).

#### Follow-up assessment of family social network survey

Approximately 2 weeks after the collection of the endpoint survey data, family members will be recontacted and the social network data will be recollected via individual phone interview (see Table 1).

### Outcome measures

The primary outcome tested will be the changes in intentions to improve food choices following exposure the FHH the main hypothesis is that exposure to the FHH will improve intended dietary behaviour with the extent of improvement dependent about the nature of risk within the family (i.e., above average v average). Secondary analyses will focus on exploration of the communication, social influence, and support networks within families at baseline, and how these differ between cultural groups and are related to health behaviors. Changes in the patterns or ‘structure’ of these social networks after exposure to the Families SHARE intervention will be compared to changes in the control families. For example, we will test if exposure to Families SHARE activates a communal coping response, evidenced by an increase in density of communication ties and encouragement ties among family members, and if this moderates health behaviour outcomes.

#### Sample size

Power analyses were conducted to estimate the number of families needed to evaluate the impact of the intervention on intentions to change diet. The sample size estimates consider potential clustering of the outcome variable in families, and is based on a multilevel generalized linear model assessing the effect of intervention (intervention vs. control; level 2 variable) on behavioural intentions at follow-up. Covariates considered within the fitted model include the baseline intentions (level 1 variable) and ethnic group (level 2 variable). Since the intervention component is a level 2 variable, the power calculations optimize the macro-level units [49]. Based on a medium effect size (Cohen’s f = .25, ω^2^ = .06), a Type I error rate of .05, we would need, conservatively, 132 families to achieve a power equal to .80. As the time between baseline and the final assessment is short, we expect retention rates to be relatively high and so an initial sample of 150 families will be recruited.

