### Statistical analyses

#### Primary outcomes

The primary outcome is change on the diet-related intentions of each individual in the study, according to group assignment (Treatment (FHH) versus Control), controlling for ethnic background (Anglo, Italian, and Vietnamese). The primary outcomes are; intentions to change diet, specifically, fruit and vegetable and fibre consumption. Secondary outcomes include intentions to change physical activity, alcohol consumption and smoking. These initial analyses will consider differential effectiveness of the intervention according to extent of family risk for chronic disease and the ethnic background of the families.

While the time period between assessments is short, which will limit potential behavioural changes over the 6-month period, levels of consumption and participation in ancillary health-linked lifestyle choices will also be assessed and compared between groups and over time. In addition, we will establish the extent to which change is moderated within the intervention group by the nature of the feedback (average v above average risk) and the potential moderating or mediating effects of cultural and social capital, health locus of control, optimism in the full sample, and acculturation within the minority groups.

A multilevel modelling approach, which accounts for participants being nested in families, will be used to look at the effect of the intervention, and ethnicity, on intentions to change behaviors post intervention. We hypothesize a main effect for the intervention condition so that intentions and behavior become more consistent with feedback recommendations following exposure to the FHH assessment than does that of the control group. Comparison between ethnic groups will test for efficacy differences.

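### The .80 power at 132 families covers the overall intervention effect, but the main hypothesis also includes dependence on family risk, which the sizing leaves out and which the plan partly assesses within the intervention arm alone

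*Protocol article*

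**What the plan says.** The Sample size section rests on a multilevel model "assessing the effect of intervention (intervention vs. control; level 2 variable) on behavioural intentions at follow-up". It adds: "Covariates considered within the fitted model include the baseline intentions (level 1 variable) and ethnic group (level 2 variable"). The inputs are given as "Based on a medium effect size" (Cohen's f = .25) and "a Type I error rate of .05", and the result is "we would need, conservatively, 132 families to achieve a power equal to .80". Recruitment is then set at 150: "we expect retention rates to be relatively high and so an initial sample of 150 families will be recruited".

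The Outcome measures section states the main hypothesis as an improvement in intended diet "with the extent of improvement dependent about the nature of risk within the family (i.e., above average v average"). The abstract likewise adds risk moderation to its primary hypothesis and places it in the treatment group.

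Under Statistical analyses, the Primary outcomes section includes in the initial analyses whether the intervention works differently by family risk and by ethnic background. Its next paragraph plans to assess moderation by type of feedback (average or above average) inside the intervention arm. It also hypothesises a main effect of the intervention, and says of ethnicity: "Comparison between ethnic groups will test for efficacy differences".

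No section labels the risk analysis as secondary or exploratory. The Outcome measures section uses the secondary label for the social network analyses.

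**The concern.** The hypothesis and the sample size describe different estimands. The sized model tests one average difference between arms. The main hypothesis also says that this difference is larger in one risk group than in the other, which is an interaction, and neither a risk variable nor an interaction enters the power calculation.

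Two things are at stake. First, a true difference between risk groups of moderate size would probably be missed. A null result beside a quoted power of .80 could then be taken to mean that risk level does not matter. Second, a comparison of risk groups among intervention families alone cannot separate a larger intervention effect from a difference that would have appeared without the intervention, because families are not randomised to risk level.

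**Working it through.** **Inputs from the protocol.** f = .25, alpha .05, power .80, 132 families needed and 150 recruited (Sample size); 50 families in each of three ethnic groups (Abstract, Methods).

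**Assumptions.** The family is the unit, allocation is 1:1, tests are two-sided, and effects are in family-level SD because no intraclass correlation is given. Risk is a family-level factor, as the main hypothesis words it. The interaction size and the share *q* of above-average-risk families are not stated, so ranges are used.

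**1. The plan's own figure.** With two equal arms, d = 2f = 0.5. The F test with 1 df has noncentrality N × f². At N = 132 this is 132 × .0625 = 8.25, and power is .81. The minimum N for .80 is 128; rounded up to equal cells in 2 arms × 3 ethnic groups it is 6 × 22 = 132. The figure reproduces.

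**2. Arm × risk, all families.** The difference between the two risk groups' intervention effects has

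SE = 2 × √(1/(Nq) + 1/(N(1 − q))) = 2 / √(N q(1 − q)).

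At N = 132 and an even split, SE = 2/√33 = 0.348. A difference of 0.5 SD gives noncentrality 0.5/0.348 = 1.44 on 128 df.

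| Risk split | SE at 132 | Power at 132, 0.5 SD | Power at 150, 0.5 SD | Difference detectable with .80 at 132 | Families for .80 at 0.5 SD |
|---|---|---|---|---|---|
| 50:50 | 0.348 | .30 | .33 | 0.98 SD | 506 |
| 70:30 | 0.380 | .26 | .29 | 1.07 SD | 600 |
| 80:20 | 0.435 | .21 | .23 | 1.23 SD | 788 |

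**3. The same f for the interaction.** For this contrast f = difference × √(q(1 − q)) / 2. At an even split f = .25 corresponds to 4 × .25 = 1.0 SD, for example effects of 0 and 1.0 SD. Power at 132 is then .81. A 0.5 SD difference corresponds to f = .125.

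**4. Main effect and risk moderation together.** With an even split, and treating the two tests as independent, power for both is .813 × .297 = .24 at a 0.5 SD difference and .813 × .813 = .66 at 1.0 SD.

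**5. Risk groups inside the intervention arm.** With 66 families and a 0.5 SD difference, SE = √(1/33 + 1/33) = 0.246 and power is .52 at an even split; at 70:30 it is .45. This is higher than in step 2 only because the corresponding difference among control families is taken to be zero instead of being estimated.

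**6. Arm × ethnicity (2 df).** At f = .25, power is .72 at 132 families and .78 at 150. For evenly spaced effects averaging 0.5 SD, the spacing is .25 × √6 = 0.61, so f = .25 means effects of about 1.11, 0.50 and −0.11 SD. Effects of 0, 0.5 and 1.0 SD give .53; effects of 0.25, 0.50 and 0.75 SD give .16.

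**The case against.** Sizing a trial on its average effect while also examining moderators is ordinary practice. The Sample size section already ties its .80 to intervention versus control, and no sentence extends it to an interaction. This stands: neither 132 nor the .80 is in error. What remains is that the main hypothesis is worded more widely than the effect that was sized.

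The low power for risk depends on an assumed 0.5 SD difference, whereas f = .25 for the interaction would give .81. This also stands as arithmetic. But at an even split it requires effects 1.0 SD apart, twice the planned effect, and the protocol gives no reason to expect that.

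Risk moderation can be read as a comparison within the intervention arm, with power of .45 to .52 and not .21 to .30. The abstract and part of the Primary outcomes section support that reading. However, that comparison does not estimate a difference in intervention effect, and the same section also speaks of effectiveness differing by family risk, which needs both arms.

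A reader might infer that the main hypothesis also requires an ethnic difference, and that the trial is too small because a 2-df test at f = .25 needs 158 families against 150 recruited. The documents do not support this. Ethnicity is absent from the main hypothesis in Outcome measures, the abstract says only that improvement may vary by ethnic background, and the background section on the proposed study and the Study aims call it a potential moderator. Nor does any section propose separate significance tests within each ethnic group.

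**Conclusion.** The concern holds in a limited form. The 132 families are adequate for the overall effect at f = .25. They do not give comparable power for the risk dependence that the main hypothesis includes: about .21 to .30 for a 0.5 SD difference in effects, with .80 reached only at about 0.98 to 1.23 SD. These figures rest on an assumed interaction size, risk splits from 50:50 to 80:20, the family as the unit and 1:1 allocation. Retaining all 150 families raises the range only to .23 to .33.

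The planned look inside the intervention arm is a separate weakness, because it gives up the control families that would make the comparison interpretable. The ethnic comparison is a lesser matter: the protocol commits to the test but presents ethnicity as a potential moderator. It would be wrong to conclude that the sample size is miscalculated or that more families must be recruited.

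**What to change.** - **Outcome measures:** limit the confirmatory hypothesis to the overall effect of the intervention on dietary intentions, and state risk moderation as a secondary question.
- **Statistical analyses, Primary outcomes:** estimate risk moderation as an arm-by-risk interaction in the full sample, reported with a confidence interval, in place of the comparison within the intervention arm. The Baseline survey section invites index parents in both arms to give their family history, so risk can be classified in control families too.
- **Sample size:** add the arm-by-risk difference detectable with .80 power at 132 families, with the assumed risk split (about 0.98 SD at 50:50, 1.23 SD at 80:20).
- **Ethnic comparison:** handle it the same way, as a secondary arm-by-ethnicity interaction with confidence intervals, consistent with its description as a potential moderator. Note that power is .72 at 132 families even at f = .25.

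The cost is rewording in three sections and weaker claims on moderation. No extra families or data are needed.

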### Statistical analyses

#### Primary outcomes

The primary outcome is change on the diet-related intentions of each individual in the study, according to group assignment (Treatment (FHH) versus Control), controlling for ethnic background (Anglo, Italian, and Vietnamese). The primary outcomes are; intentions to change diet, specifically, fruit and vegetable and fibre consumption. Secondary outcomes include intentions to change physical activity, alcohol consumption and smoking. These initial analyses will consider differential effectiveness of the intervention according to extent of family risk for chronic disease and the ethnic background of the families.

While the time period between assessments is short, which will limit potential behavioural changes over the 6-month period, levels of consumption and participation in ancillary health-linked lifestyle choices will also be assessed and compared between groups and over time. In addition, we will establish the extent to which change is moderated within the intervention group by the nature of the feedback (average v above average risk) and the potential moderating or mediating effects of cultural and social capital, health locus of control, optimism in the full sample, and acculturation within the minority groups.

A multilevel modelling approach, which accounts for participants being nested in families, will be used to look at the effect of the intervention, and ethnicity, on intentions to change behaviors post intervention. We hypothesize a main effect for the intervention condition so that intentions and behavior become more consistent with feedback recommendations following exposure to the FHH assessment than does that of the control group. Comparison between ethnic groups will test for efficacy differences.

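### The primary analysis is described inconsistently: only the sample-size section names baseline intention as a covariate, while the outcome is elsewhere defined as change

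*Protocol article*

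**What the plan says.** Three places in the Protocol article bear on the primary analysis.

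- **Sample size.** The powered model is a multilevel generalized linear model "assessing the effect of intervention (intervention vs. control; level 2 variable) on behavioural intentions at follow-up". Its adjustment is given as "Covariates considered within the fitted model include the baseline intentions (level 1 variable) and ethnic group (level 2 variable".
- **Outcome measures.** The primary outcome is described as changes in intentions about food choices.
- **Statistical analyses, Primary outcomes.** The definition is "The primary outcome is change on the diet-related intentions of each individual in the study, according to group assignment", with ethnic background as the only adjustment named. The dietary areas are fruit and vegetable consumption and fibre consumption. Later in the section, a multilevel model "will be used to look at the effect of the intervention, and ethnicity, on intentions to change behaviors post intervention".

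Table 1 (Section 3, intended lifestyle changes) shows how intention is recorded. There is an opening item, "Considering Lifestyle change (yes or no". Those who answer yes then identify each area of change and rate their confidence on a 7-point scale. Fruit and vegetable intention is asked of adults and children; fibre intention is asked of adults only. Both are collected at baseline and endpoint.

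**The concern.** Read literally, these passages allow three analyses of the same data: follow-up intention adjusted for baseline, a change in intention, and follow-up intention without baseline. They can give different estimates and p-values. A reader cannot tell from the article which one is primary, and the registration was retrospective, so the article's own wording carries more weight than usual.

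Precision is also at stake. Families are allocated from a simple randomisation list within ethnic group, so a chance imbalance in baseline intention is possible. Among the three descriptions, only the sample-size model names baseline intention as a covariate. An analyst who followed the Primary outcomes section to the letter would give up precision that the trial has already paid for by measuring intention at baseline.

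**Working it through.** **Inputs from the Sample size section.** Effect size: "Based on a medium effect size (Cohen’s f = .25, ω^2^ = .06"). Error rate, power and number: "a Type I error rate of .05, we would need, conservatively, 132 families to achieve a power equal to .80".

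**Assumed, because the article does not give them.** A two-sided (F) test, 1:1 allocation, equal variance at baseline and follow-up, and the correlation r between family-level baseline and follow-up intention. The outcome is treated as continuous at family level.

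**Step 1: reproduce 132.** Use a noncentral F test with 1 numerator df, families as units and noncentrality λ = N × f². With f = .25, N = 128 is the smallest number that reaches .80. Rounded up to a multiple of 6 (three ethnic groups by two arms) this is 6 × 22 = 132. The rounding is an inference, but it fits the figure exactly. At N = 132, λ = 132 × .0625 = 8.25 and power is .813. No variance reduction from baseline is needed to reach this.

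**Step 2: relative variance of the three analyses.** In units of the follow-up variance:

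- follow-up only: 1
- change score: 2(1 − r)
- baseline-adjusted: 1 − r²

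Change against adjusted is 2(1 − r)/(1 − r²) = 2/(1 + r). Follow-up only against adjusted is 1/(1 − r²). Both ratios exceed 1 for every r between 0 and 1.

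| r (assumed) | change / adjusted | follow-up only / adjusted |
|---|---|---|
| .3 | 2/1.3 = 1.54 | 1/.91 = 1.10 |
| .5 | 2/1.5 = 1.33 | 1/.75 = 1.33 |
| .7 | 2/1.7 = 1.18 | 1/.51 = 1.96 |

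**Step 3: power at 132 families.** The answer depends on which standard deviation f = .25 refers to.

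*Reading A: f is on the unadjusted SD.* Then λ is 8.25 for follow-up only, 8.25/[2(1 − r)] for change, and 8.25/(1 − r²) for adjusted.

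| r | follow-up only | change | adjusted |
|---|---|---|---|
| .3 | .813 | .673 | .848 |
| .5 | .813 | .813 | .908 |
| .7 | .813 | .957 | .979 |

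*Reading B: f is on the baseline-adjusted residual SD.* Then λ is 8.25 for adjusted, 8.25(1 + r)/2 for change, and 8.25(1 − r²) for follow-up only.

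| r | follow-up only | change | adjusted |
|---|---|---|---|
| .3 | .776 | .632 | .813 |
| .5 | .695 | .695 | .813 |
| .7 | .530 | .748 | .813 |

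The adjusted model has the highest power in every row of both tables. Whether the others fall below .80 depends on the reading and on r. Under A, follow-up only never does, and the change score does so only for r below about .5. Under B, both do at each r shown.

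**The case against.** The strongest reply is that nothing has been dropped. The Sample size section calls the baseline-adjusted model the one to be fitted. The single model sentence under Primary outcomes is also multilevel and also concerns intentions after the intervention. It does not repeat the baseline covariate, but it neither excludes it nor claims to be a full list. Change may be a loose label for follow-up adjusted for baseline; no passage says that a difference is the dependent variable. A condensed article can also leave a covariate list to the analysis plan. This stands as far as it goes: a deliberate removal of the covariate is not shown. It does not make the wording consistent, because the outcome label and the named adjustment still differ between sections of the same article.

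A reader might infer that the trial is underpowered, or that the .80 belongs to the adjusted model alone. The article does not support either. The figure of 132 reproduces with no credit for baseline, which fits the authors' description of it as conservative, and the low power values need both Reading B and an assumed r.

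A reader might also infer that a change score is specifically biased, because someone who already intends to change cannot improve and because of regression to the mean. The ceiling belongs to the item and limits an endpoint model equally. Regression to the mean is, in expectation, the same in both randomised arms; it costs precision and does not bias the contrast.

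Finally, the item is a yes/no choice, so the continuous formulas do not carry over directly to a logistic model, in which baseline adjustment also changes the odds ratio being estimated. The figures indicate direction and rough size only.

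**Conclusion.** The inconsistency is real and concerns the definition of the primary test. For any r that is positive and below 1, the model in the Sample size section is more precise than either analysis that could be read from the Primary outcomes section. Against a change score the variance ratio runs from 1.54 to 1.18 for assumed r of .3 to .7. On the raw-SD reading at r = .5, power is .81 for either unadjusted analysis and .91 with adjustment.

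No shortfall against the planned .80 can be established, since r and the scale of f are not stated. The result rests on equal variances over time, 1:1 allocation, a two-sided test and a continuous family-level approximation to a yes/no item. The point is therefore a contradiction to reconcile, with a gain in precision at no cost, and not a demonstrated loss of planned power.

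**What to change.** In Statistical analyses, Primary outcomes, state one primary model that matches the Sample size section:

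- **Outcome:** endpoint intention for each named dietary area, namely fruit and vegetables in all participants, and fibre in adults, the only group asked about it.
- **Model:** multilevel generalized linear model with a family random intercept, logistic if the area item is analysed as yes/no.
- **Terms:** arm, the same area item at baseline, and ethnic group.

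Replace change as the outcome definition there, and align the label under Outcome measures. Say that the outcome is the area-specific item, so that it is not confused with the opening yes/no question or the confidence rating. It would also help to state in the Sample size section which SD the effect size refers to.

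The cost is wording only. Table 1 already collects these items at baseline from everyone to whom they apply, and neither the sample size nor the survey changes.
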